## Abstract

**Background:**

Diabetic Peripheral Neuropathy (DPN) can markedly diminish patients’ quality of life. Current treatments provide limited relief, driving interest in non-invasive options such as moxibustion. Moxibustion, a technique rooted in acupuncture, shows promise for managing pain. However, it lacks standardized protocols for treating DPN, especially concerning moxibustion duration, and its effectiveness for DPN is not well-supported by evidence. Thus, this study seeks to identify the optimal moxibustion duration to relieve DPN symptoms and enhance nerve function, filling an important gap in clinical practice.

**Methods:**

Participants will be randomly allocated to three clinical centers, with 30 individuals at each center, and evenly divided among the conventional treatment group, the 15-min moxibustion group, and the 30-min moxibustion group. The conventional treatment group will be administered mecobalamin and epalrestat for a duration of 4 weeks, while the moxibustion groups will receive moxubustion as an add-on therapy treatment twice a week over the same period. The duration of moxibustion differs from the 15-min group, while the procedure remains consistent across the moxibustion groups. The primary outcome is total clinical effectiveness. The second outcomes include electrophysiological examination, the Toronto Clinical Scoring System (TCSS), the Visual Analogue Scale (VAS), the Traditional Chinese Medicine Syndrome Score Scale (TCMS), and infrared thermography testing. The outcomes will be assessed during the baseline period, after the 8th treatment, and at the one-month follow-up.

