### Study design

2.1

This trial is a multi-clinical center, open method, randomized controlled trial (RCT), three-arm, parallel-group design. The study is designed to assess moxibustion as an add-on therapy to conventional treatment. This study protocol obtained approval from the Ethics Committee of the Third Hospital Affiliated with Zhejiang University of Traditional Chinese Medicine and has been registered with the Clinicaltrials registry (identification code: NCT06330233). This trial protocol is developed in accordance with the Standard Protocol Items: Recommendations for Interventional Trials (SPIRIT) guideline. The schedule of this trial is presented in Table 1, and the flow diagram of the study is shown in Figure 1.

**Table 1 tab1:** Schedule of enrolment, interventions and outcome assessments.

Study period	Baseline	Treatment phase (4 weeks)		Follow-up phase (1 month)
The time point	Week 0	Week 2	Week 4	month 1
Eligibility screening	√			
Demographic information	√			
Case data	√			
Inclusion criteria	√			
Exclusion criteria	√			
Moxibustion treatment		√	√	
Outcomes assessment				
(1) Total clinical effectiveness			√	√
(2) Electrophysiological examination	√		√	
(3) TCSS	√		√	√
(4) VAS	√		√	√
(5) TCMS	√		√	√
(6) Infrared thermography testing	√		√	
Safety evaluation		√	√	

√, required; TCSS, Toronto Clinical Scoring System; VAS, visual analog scale; TCMS, traditional Chinese medicine syndrome score scale.

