### Participant recruitment

2.2

Eligible DPN patients will be recruited from the Third Affiliated Hospital of Zhejiang Chinese Medical University, the First Affiliated Hospital of Zhejiang Chinese Medical University, and the Zhejiang Greentown Cardiovascular Hospital. Each participant will be provided with a detailed procedure description before signing the informed consent form.

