### Randomization and allocation concealment

2.7

Participants eligible for inclusion will be randomly assigned to three groups: the conventional treatment group, the moxibustion 15-min group, and the moxibustion 30-min group. An impartial administrator, not engaged in other study operations, will carry out this process, and the details of the random allocation list will remain absolutely confidential. The random allocation sequence will be computer-generated with a 1:1:1 ratio using the Electronic Data Capture System of Zhejiang Chinese Medical University.

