#### Statistical analysis

2.10.3

Statistical analysis of the data will be performed by a third-party statistician who will not involved in the pre-test, using the statistical software IBM SPSS Statistics version number (SPSS 26.0). Measurement information to meet the normal distribution of the use of the mean ± standard deviation table, counting information is expressed in the number of cases (%). The non-parametric rank sum test was employed for group comparisons, while chi-square analysis will facilitate additional group comparisons. Furthermore, a mixed linear model, COX regression analysis, and logistic regression analysis will be utilized for the exploratory examination of factors influencing the primary outcome indices. For missing data handling, multiple imputation will be employed for primary outcome analyses. A *p*-value of less than 0.05 indicates that the differences are statistically significant. Statistical analyses will be conducted by qualified statisticians. Upon completion of data entry and review, statisticians must finalize the statistical analysis promptly and produce a written report detailing the findings.

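### The abstract has patients randomly allocated to centres and split evenly at each; the body recruits at the centres and states no centre stratum that would give that split

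*Protocol article*

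**What the plan says.** The abstract (Methods) states: "Participants will be randomly allocated to three clinical centers, with 30 individuals at each center, and evenly divided among the conventional treatment group". The sentence goes on to the 15-minute and 30-minute moxibustion groups.

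The body describes something else:

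- Section 2.2 (Participant recruitment) names three hospitals as the source of patients: "Eligible DPN patients will be recruited from the Third Affiliated Hospital", followed by the other two.
- Section 2.7 (Randomization and allocation concealment) makes treatment the thing that is randomised: "Participants eligible for inclusion will be randomly assigned to three groups". It adds: "The random allocation sequence will be computer-generated with a 1:1:1 ratio". It names no stratification by centre and no blocks. It does say that an independent administrator runs the process and that the list is kept confidential.
- Section 2.10.4 (Sample size estimation) gives 30 per group and 90 in total. The body does not repeat the 30 per centre.
- Section 2.10.3 (Statistical analysis) says: "The non-parametric rank sum test was employed for group comparisons, while chi-square analysis will facilitate additional group comparisons". Regression models are listed for exploratory use only. Centre is not mentioned.

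**The concern.** Two things do not fit together.

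First, the abstract and the body disagree on what is randomised. A patient recruited at a hospital has not been randomly allocated to it. Taken literally, the abstract describes a different design from the one in 2.2 and 2.7.

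Second, 30 per centre divided evenly over three groups reads most naturally as 10 per arm within each centre. An exact split of that kind needs allocation to be restricted within each centre. The method printed in 2.7 states only an overall 1:1:1 ratio, which does not secure it.

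This matters because moxibustion depends on the operator. Section 2.9.2 has the practitioner hold the moxa at a distance judged by the patient's sensation of warmth, and the Discussion acknowledges that the technique is not standardised. Operators and case mix may well differ between hospitals. With about 10 patients per arm at a centre, a gap of 6 between arms could mix centre differences into the treatment comparisons, including 15 against 30 minutes, which is the trial's main question.

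**Working it through.** **Inputs.** Three centres of 30 (abstract), three arms at 1:1:1 (2.7), 30 per arm and 90 in total (2.10.4). The documents do not say how the sequence is restricted, so three cases are shown.

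**Case A: simple randomisation (assumption).**
- One given centre: P(10/10/10) = 30! / (10!³ × 3³⁰) = 0.0270, or 2.7%.
- All three centres: 0.0270³ ≈ 0.00002, or 0.002%.
- One given centre, largest arm minus smallest arm at least 6: summing the multinomial probabilities gives 0.429.
- At least one of three centres: 1 − (1 − 0.429)³ = 0.814, or 81%.

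**Case B: one fixed list of 30 per arm shared by the centres, with no centre stratum (assumption).**
- First centre: P(10/10/10) = C(30,10)³ / C(90,30) = 0.0403.
- Second centre, given the first: C(20,10)³ / C(60,30) = 0.0533. The third is then fixed.
- All three centres: 0.0403 × 0.0533 = 0.0021, or about 0.2%. Simulating shared permuted blocks of 3, 6 or 9 (40,000 runs each) gives practically the same result, 0.0019 to 0.0022.
- At least one centre with arms differing by 6 or more: 0.54, by enumerating all tables with 30 per arm and 30 per centre.

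**Case C: permuted blocks within each centre, of a fixed size dividing 30 (for example 3 or 6).** A full centre of 30 is 10/10/10 with certainty.

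| Case | 10/10/10 in all three centres | Some centre with arms differing by 6 or more |
|---|---|---|
| A. Simple | 0.002% | 81% |
| B. Fixed 30/30/30 list, not stratified | 0.2% | 54% |
| C. Fixed blocks within centre | 100% | 0% |

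Of these three, only the case with a centre stratum makes the abstract's statement true, and 2.7 does not state such a stratum.

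**The case against.** The strongest reply is that this is loose wording in an abstract. The body states the unit of randomisation clearly, and nobody running the trial would randomise patients to hospitals. Strata and block sizes are details that a journal article often leaves to the full protocol. Section 2.7 never says that the sequence is single or unstratified, and centre-stratified blocks in the EDC would fit both the abstract and 2.7. Nor is 10/10/10 printed: the even division could refer to the 90 patients overall, which agrees with 30 per group in 2.10.4.

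Most of this stands, and it limits the point. The missing stratum is not a defect by itself. What remains is that the abstract makes a statement that the body contradicts on the unit of allocation and does not support on within-centre balance. The fixed-list case shows that this does not depend on assuming simple randomisation.

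Three stronger readings are tempting and are not supported:

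- A reader might infer that staff in this open trial can work out the last allocations at a site. That presumes a known quota enforced in a visible way. The documents do not describe this, and 2.7 says that the list is confidential.
- A reader might infer that leaving centre out of the analysis is a separate error. The article is condensed and the statistical analysis plan is not shown, so silence in 2.10.3 does not establish that.
- A reader might want to put a figure on the precision lost without centre adjustment. The documents give no centre-specific response rates, so any such figure would rest on invented inputs.

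**Conclusion.** The contradiction between the abstract and sections 2.2 and 2.7 is established and must be reconciled. The even split within centres is the natural but not the only reading. On that reading, the method as printed does not support it. Without a centre stratum, the chance of the split in all three centres is 0.002% to 0.2%, and a gap of 6 or more patients in at least one centre occurs in 54% to 81% of trials.

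Those ranges assume exactly 30 patients per centre and no stratification. If the EDC already randomises within centre using fixed blocks that divide 30, the imbalance is nil and only the text is wrong. The article does not let the reader tell which situation holds.

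**What to change.** 1. Reword the abstract along these lines: *participants will be recruited at three centres (30 each) and randomised 1:1:1 within centre to the three groups*.
2. In 2.7, state that randomisation is stratified by centre, with randomly varied block sizes (for example 3 and 6) concealed from the sites.
3. In 2.10.3, analyse the primary responder outcome with a centre-stratified test, such as Cochran-Mantel-Haenszel, in place of the unstratified chi-square, so that the analysis follows the randomisation.

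The cost is an EDC setting, if it is not already in place, and three changes of wording. The total stays at 90. The downside is that varied blocks may leave a centre one or two patients off an exact even split. For example, 27 patients in complete blocks give 9 per arm. If the last three come from an unfinished block of 6, which holds two places per arm, the centre ends at 10/10/10 or at worst 11/10/9. If the EDC already stratifies by centre, items 1 and 2 only describe what is being done.

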**Conclusion:**

This trial aims to identify the optimal moxibustion duration for DPN symptom relief and nerve function improvement, offering evidence for standardized clinical protocols. The findings could enhance treatment efficacy, reduce adverse effects, and alleviate DPN’s socio-economic burden.

**Clinical trial registration:**

https://clinicaltrials.gov/, NCT06330233.

## Introduction

1

Diabetic peripheral neuropathy (DPN) is one of the most common chronic complications of diabetes. Epidemiological survey results suggest that diabetes ranks as the third chronic non-communicable disease posing a significant threat to human health, following tumors and cardiovascular and cerebrovascular diseases (1, 2). By 2030, it is projected that the global population of people with diabetes will reach 643 million, with China currently having 114 million adult diabetic patients or 24% of the worldwide diabetic population (1). The primary symptoms of DPN are numbness, paresthesia, freezing and burning sensations, pain, and other reactions in the distal feet and toes, resulting in significant physical and emotional distress for patients (3, 4).

Currently, western treatment for DPN is limited in its ability to alleviate clinical symptoms (5–7) and frequent adverse effects., hence elevating the risk of impairment and significantly impacting patients’ quality of life (8). Moreover, these pharmacological interventions often necessitate prolonged use, increasing treatment burden and posing challenges to patient adherence. Consequently, these shortcomings underscore an urgent need for optional, safe, and effective therapeutic strategies to enhance clinical outcomes in DPN.

Acupuncture therapy is a traditional Chinese medical practice that entails the insertion of needles into certain points on the body to stimulate and treat various diseases (9–11). From an evidence-based perspective, acupuncture can modulate the nervous system and other physiological processes to produce theraputic effects like pain relief (12–15). A meta-analysis reveals that acupuncture, when combined with conventional treatment, successfully alleviates discomfort associated with DPN (16). Our early research concentrated on the fundamentals of acupuncture analgesia (17, 18), as well as a clinical study on the difference in moxibustion-induced microcirculatory responses in different meridians (19). In terms of clinical practice, moxibustion is similar to acupuncture, can treat DPN, considerably improve patients’ symptoms, and has few side effects (16, 20). Moxibustion is a supplementary and alternative therapy in which mugwort is burned at certain acupoints to offer warming stimulation for treatment and recovery (21, 22). From an evidence-based viewpoint, moxibustion potentially exerts effects through thermal stimulation that may influence local circulation and neural pathways (23–25). Moxibustion on appropriate acupoints in DPN patients can successfully improve local neurotrophic symptoms, improve nerve cell function, boost sensitivity and nerve conduction velocity, and have significant therapeutic effects (19, 26).

Emerging clinical evidence suggests that moxibustion can alleviate DPN-associated pain and numbness (20). However, its therapeutic protocols remain unstandardized, particularly with respect to treatment duration. Existing studies report a wide range of moxibustion durations—from a few minutes to as long as 30 min—with little consensus on the optimal timeframe or its impact on efficacy. This gap in knowledge hinders the broader adoption and optimization of moxibustion as a viable treatment for DPN.

Therefore, we hypothesize that the combination of moxibustion and conventional treatment for diabetic peripheral neuropathy is more efficacious than conventional treatment alone. Nonetheless, the distinction in efficacy between the 15-min moxibustion group and the 30-min moxibustion group necessitates further investigation.

To address this critical research gap, this randomized controlled trial aims to evaluate the effects of varying moxibustion durations (15 min vs. 30 min) on symptom relief and nerve function improvement in patients with DPN. By identifying the optimal duration of moxibustion, this research seeks to provide evidence-based guidance for the clinical management of DPN and advance the standardization of moxibustion therapy.

## Methods and analysis

2

### Study design

2.1

This trial is a multi-clinical center, open method, randomized controlled trial (RCT), three-arm, parallel-group design. The study is designed to assess moxibustion as an add-on therapy to conventional treatment. This study protocol obtained approval from the Ethics Committee of the Third Hospital Affiliated with Zhejiang University of Traditional Chinese Medicine and has been registered with the Clinicaltrials registry (identification code: NCT06330233). This trial protocol is developed in accordance with the Standard Protocol Items: Recommendations for Interventional Trials (SPIRIT) guideline. The schedule of this trial is presented in Table 1, and the flow diagram of the study is shown in Figure 1.

**Table 1 tab1:** Schedule of enrolment, interventions and outcome assessments.

Study period	Baseline	Treatment phase (4 weeks)		Follow-up phase (1 month)
The time point	Week 0	Week 2	Week 4	month 1
Eligibility screening	√			
Demographic information	√			
Case data	√			
Inclusion criteria	√			
Exclusion criteria	√			
Moxibustion treatment		√	√	
Outcomes assessment				
(1) Total clinical effectiveness			√	√
(2) Electrophysiological examination	√		√	
(3) TCSS	√		√	√
(4) VAS	√		√	√
(5) TCMS	√		√	√
(6) Infrared thermography testing	√		√	
Safety evaluation		√	√	

√, required; TCSS, Toronto Clinical Scoring System; VAS, visual analog scale; TCMS, traditional Chinese medicine syndrome score scale.

**Figure 1 fig1:**
[figure not shown]
Flow chart of the study process.

### Participant recruitment

2.2

Eligible DPN patients will be recruited from the Third Affiliated Hospital of Zhejiang Chinese Medical University, the First Affiliated Hospital of Zhejiang Chinese Medical University, and the Zhejiang Greentown Cardiovascular Hospital. Each participant will be provided with a detailed procedure description before signing the informed consent form.

### Diagnosis criteria

2.3

The diagnostic criteria for DPN, established in accordance with Chinese recommendations (27), are delineated as follows.

A clear history of Type 2 diabetes mellitus.Peripheral neuropathy that appeared at the time of or after the diagnosis of diabetes mellitus.Clinical symptoms (pain, numbness, sensory abnormalities, etc.) and signs are consistent with the presentation of DPN.Abnormalities in any of the 5 tests (ankle reflex, pinprick nociception, vibration sensation, pressure sensation, temperature sensation).Or in the absence of clinical symptoms, any two of the 5 tests are abnormal.Rule out other diseases that cause peripheral neuropathy. Identify neurotoxic effects caused by drugs, especially chemotherapeutic drugs, and neurological damage caused by metabolic poisons due to renal insufficiency.

### Inclusion criteria

2.4

History of diabetes mellitus.Persistent pain and/or sensory abnormalities in the extremities (at least in both lower limbs), decreased bilateral or unilateral ankle reflex, decreased vibration sensation (medial ankle is weaker than medial tibial condyle), decreased nerve conduction velocity on the affected side, TCSS score > 5.18 years ≤ age ≤ 80 years.Gender is not limited.Those who have the ability of independent in daily life and can cooperate to complete all the examinations.Those who are conscious without serious mental diseases and cognitive disorders, and those who do not have serious cardiac, cerebral, hepatic, renal, and other internal diseases.Voluntary participation and signing of informed consent.

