#### Secondary outcomes

2.10.2

Electrophysiological examination

The electrophysiological examination will be detected at week 0 and after 4 weeks of treatment (week 4). The latency, amplitude, motor nerve conduction velocity (MNCV), and sensory nerve conduction velocity (SNCV) of the tibial nerve and peroneal nerve of the lower extremities will be measured before and after treatment.

Toronto Clinical Scoring System (TCSS)

The TCSS is a valid instrument to reflect the presence and severity of diabetic peripheral sensorimotor polyneuropathy as measured by sural nerve morphology and electrophysiology (29). TCSS will be estimated at week 0, week 4, and month 1.

Visual Analogue Scale (VAS)

The level of pain at the subject’s lesion site will be determined using the VAS scale, which classifies pain on a scale of 0–10, with the greater the number the more pronounced the pain, i.e., a score of 0 indicates no pain, 1–3 represents mild pain, 4–6 represents moderate pain, 7–9 represents severe pain, and 10 represents severe pain. Participants will be allowed to indicate the level of pain by crossing out specific numbers on the scale according to their actual situation. The VAS scale will be administered at week 0, week 4, and month 1.

Traditional Chinese Medicine Syndrome Score Scale (TCMS)

The evaluation of the curative effect of TCMS should refer to the guiding principles of clinical research of new drugs of traditional Chinese medicine and the clinical evidence-based practice guide of traditional Chinese medicine for diabetes. TCMS will be estimated at week 0, week 4, and month 1.

The specific records are as follows:

The VAS score of limb pain was consistent according to the severity.The three main traditional Chinese medicine syndromes of limb numbness, abnormal chill (or fever), and ant feeling were scored as 0, 1, 2, and 3 points, respectively, according to their severity.

Infrared thermography

The test sites will be bilateral plantar, dorsal, palmar, and dorsal hands. The instrument used is the NECR450 infrared thermal imager produced by NECAVIO Company in Japan. Infrared thermography testing will be performed once at week 0 and once at week 4.

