## Conclusion

4

This study protocol aims to determine the optimal duration of moxibustion treatment for diabetic peripheral neuropathy through a rigorous multicenter randomized controlled trial design. By comparing 15-min and 30-min moxibustion durations as add-on therapies to conventional treatment, this research will provide evidence-based guidance for clinicians and contribute to the standardization of moxibustion protocols for DPN management. The expected outcomes include improved clinical effectiveness rates, enhanced nerve function parameters, and reduced neuropathic pain, which collectively may lead to better quality of life for DPN patients and reduced healthcare burden.

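### The pain VAS comparison is not limited to patients who have pain at entry, so under the stated rank sum test its effect is diluted and power is lost on a secondary outcome

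*Protocol article*

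**What the plan says.** All references are to the protocol article.

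- **Entry.** Section 2.4 admits patients with "Persistent pain and/or sensory abnormalities in the extremities (at least in both lower limbs". The other conditions there (ankle reflex, vibration sense, conduction velocity, TCSS above 5) do not require pain either. The diagnostic criteria in section 2.3 go further: "Or in the absence of clinical symptoms, any two of the 5 tests are abnormal". Section 2.4 still asks for pain or a sensory abnormality, so the point rests on its and/or alone.
- **Scale.** Section 2.10.2 scores VAS from 0 to 10, where "a score of 0 indicates no pain".
- **Who is measured.** "The VAS scale will be administered at week 0, week 4, and month 1". Table 1 gives the same schedule for everyone.
- **Who is analysed.** Section 2.6 defines entry to the efficacy analysis by sessions received (four or more), with no pain condition.
- **Test.** Section 2.10.3: "The non-parametric rank sum test was employed for group comparisons". It does not say whether the test uses the week-4 score or the change from week 0, and it sets no pain restriction.
- **Expected results.** Section 4 lists "enhanced nerve function parameters, and reduced neuropathic pain".
- **Related outcome.** The limb-pain item of the TCMS follows the VAS: "The VAS score of limb pain was consistent according to the severity".

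**The concern.** A patient who enters with numbness and no pain has VAS 0 at week 0. That patient can stay at 0 or get worse, but cannot show a benefit. Such patients add the same near-zero result to every arm. The mean difference shrinks by their share, and they form a block of ties that weakens a rank comparison.

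Two things are at stake. A real pain benefit over conventional treatment could be missed, or a small average change could be read as a weak treatment when it partly reflects how many patients had no pain to treat. The comparison of 15 with 30 minutes is the more exposed if, as seems likely, that difference is the smaller one. The TCMS pain item has the same floor. The limitations in section 3 note that VAS does not capture the qualities of neuropathic pain, but not that enrolled patients may have none.

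**Working it through.** **No plan figure to reproduce.** Section 2.10.4 sizes the trial on the effectiveness rate only. The article gives no VAS effect, SD, power or share of patients with pain. All such values below are assumptions.

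**Step 1: dilution of the mean difference.** Let p be the share with pain and D the effect in patients with pain. If pain-free patients stay at 0:

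all-patient difference = p × D

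The simulation in step 2 assumes, for patients with pain, baseline mean 5 and SD 1.8, a common fall of 1 point, an extra fall of 1.5 on moxibustion and noise SD 1.8. The floor at 0 cuts the realised D to about 1.35. The formula then gives 0.50 × 1.35 = 0.68, 0.65 × 1.35 = 0.88 and 0.80 × 1.35 = 1.08. The simulated differences were 0.69, 0.88 and 1.07.

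**Step 2: power by simulation.** 30 per arm, two-sided 0.05, all patients against patients with pain from the same enrolment:

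| Analysis | 50% with pain | 65% | 80% | Loss (points) |
|---|---|---|---|---|
| Rank sum, post-treatment score | 14 vs 31% | 21 vs 39% | 33 vs 47% | 17 / 18 / 14 |
| Rank sum, change from week 0 | 34 vs 53% | 46 vs 64% | 64 vs 74% | 19 / 18 / 10 |
| Linear model adjusted for week-0 VAS | 53 vs 54% | 65 vs 66% | 75 vs 76% | 1 / 1 / 1 |

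I repeated these runs (4,000 per scenario) and every figure agreed within about 2 points. At 95% with pain the repeat gave 50.5 vs 54.1% on the post-treatment score and 80.0 vs 82.0% on change. A smaller run of 2,000 gave 50 vs 56% on the post-treatment score. The loss there is therefore about 5 points or less, allowing for simulation error.

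With 24 per arm, the evaluable number in section 2.10.4, the post-treatment score gives 11/17/27% against 24/33/39%, a loss of 13/16/12 points.

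**Step 3: check with a different model.** Let q = 1 − p be the pain-free share. Patients with pain change by a mean of 1 (control) or 2.8 (moxibustion, so D = 1.8), with SD 2; pain-free patients change by 0; 24 per arm. The variance in an arm with mean change m is p × SD² + p × q × m². At q = 0.30:

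- difference = 0.7 × 1.8 = 1.26
- control variance = 0.7 × 4 + 0.21 × 1 = 3.01
- moxibustion variance = 0.7 × 4 + 0.21 × 2.8² = 4.45
- SE = √((3.01 + 4.45)/24) = 0.557
- power = Φ(1.26/0.557 − 1.96) = Φ(0.30) = 62%

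Patients with pain only, 0.7 × 24 = 16.8 per arm: power = Φ(1.8/(2 × √(2/16.8)) − 1.96) = Φ(0.65) = 74%.

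The loss at the same enrolment is 74 − 62 = 12 points. A rank sum simulation on change under the same assumptions gives 53% against 67%, a loss of 14 points.

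**The case against.** **The low power comes mostly from ignoring baseline.** This stands. With every patient in pain, the rank sum test on the raw post-treatment score reaches only 57%, against 85% on change. A reader might take 14% to 33% as the price of admitting pain-free patients; only the gap to the matching pain-only figure is. With baseline adjustment the gap nearly vanishes. The stated test for group comparisons is a rank sum test, however. Section 2.10.3 does not commit the VAS comparison to baseline adjustment, and the rank test on change still loses 10 to 19 points.

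**Analysis in all patients is inferred.** Also fair. The article nowhere says in so many words that VAS is analysed in everyone. The reading rests on the absence of any restriction in sections 2.6, 2.10.2 and 2.10.3, and an analysis plan not at hand could add one.

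**The populations do not conflict.** A reader might infer that the entry criteria contradict the pain outcome, or that the all-patient difference describes nobody. The documents do not support either. The trial studies DPN, not painful DPN, and the introduction lists pain among several symptoms. Measuring one symptom in a mixed population is ordinary, the average over all randomised patients is a legitimate estimand, and newly arising pain is information. What remains is that this average understates the effect in patients with pain.

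**Limited reach.** VAS is one of five secondary outcomes. Neither the sample size nor the primary conclusion depends on it.

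**Conclusion.** The point holds as a matter of dilution and precision on a secondary outcome. It is not an error in the trial's main comparison. Section 2.4 admits patients at the VAS floor, no passage restricts the comparison, and the stated test then loses power whenever some patients are pain-free.

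The amount cannot be fixed from the article. Under the step 2 assumptions it runs from about 5 points or less at 95% with pain to 14 to 18 points (post-treatment score) or 10 to 19 points (change) at 50% to 80%. It is about 1 point with baseline adjustment. Baseline adjustment recovers the power but not the interpretation: the all-patient estimate is still p × D. That is why both parts of the fix are needed. It is worth doing because the cost is small.

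**What to change.** Add to sections 2.10.2 and 2.10.3, before any outcome data are seen:

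- VAS is compared between groups in patients with week-0 VAS of at least 1, using change from week 0 or adjustment for week-0 VAS, not the raw post-treatment score.
- The same comparison in all randomised patients is shown alongside.
- The number with week-0 VAS 0 is reported by arm.
- Conclusions on pain are worded as applying to patients with pain at entry.

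The subset is defined by a baseline value, so the comparison stays randomised, provided that week-0 VAS is recorded before the patient learns the allocation. Chosen after the results are known, it would be a post-hoc subgroup.

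Cost: a few sentences, with no new data, visits or patients. The downside is a smaller number in the VAS comparison; in the scenarios run with pain-free patients, power was nevertheless no lower than in all patients.
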